### Outcome measurements

#### Primary and secondary outcomes

The primary outcome is systolic blood pressure assessed using American Heart Association (AHA) guidelines [30]. Secondary outcomes include diastolic blood pressure [30], anthropometric measurements [29] (height, weight, waist circumference), fasting blood glucose and insulin, flow mediated dilation (FMD) [31], gait speed (assessed using a 16-foot GAITRite computerized walkway system, CIR Systems, Havertown, PA, USA), and accelerometer-determined physical activity and sedentary behavior. Additional protocol details for flow mediated dilation, gait speed, and accelerometry follow.

### Flow mediated dilation (FMD)

FMD will be used to determine endothelium-dependent dilation of the brachial artery. All FMD measurements will occur in the morning at approximately the same time of day at pre-intervention and post-intervention. Upon arrival to the research center, participants will rest quietly for 15 minutes supine in a hospital bed in a temperature controlled room. Brachial artery assessments will be obtained using 2D and Doppler ultrasound measurements, placed over the brachial artery in the elbow area on the non-dominant arm, with a 7.5 MHz linear array transducer and the brachial artery mean blood velocity will be measured using a pulse-wave Doppler with on-line angle correction and analysis software. When an optimal view of the brachial artery is obtained where the anterior and posterior borders of the endothelium are clearly visible, baseline images (each during a different cardiac cycle) will be taken to determine resting brachial diameter. Following completion of all baseline measurements, the blood pressure cuff will be inflated to 200 mmHg using a rapid inflation/deflation pneumatic cuff around the forearm, and held for 5 minutes in order to occlude the brachial artery. After this period of ischemia, the blood pressure cuff will be rapidly deflated, and images of the brachial artery diameter and blood flow velocity measurements will occur approximately every 5 seconds for 2 minutes. All brachial artery images are analyzed using a custom designed edge-detection and wall tracking software (Brachial Analyzer, Medical Imaging Applications, Iowa City, Iowa.).

### Gait speed

Gait variables (e.g., speed, cadence) will be assessed using the GAITRite computerized walkway system. Participants will be given a 2-meter acceleration and deceleration zone on either end of the walkway and two practice trials before performing the tested conditions. Participants will then be asked to perform two crossings at six self-selected walking speeds: very slow, slow, preferred/normal, fast, very fast, and as-fast-as-you-can (without running). The first set of crossings will always be at the preferred/normal speed. The remaining sets will be counter-balanced between those that are progressively faster than preferred/normal and those that are progressively slower. Rest will be provided as necessary. Outputs will be averaged for the two crossings within each speed set.

### Accelerometry

The selected accelerometer, the ActiGraph GT3X+, is the most widely used accelerometer in ambulatory monitoring research and will be used in WalkMore to detect minute-by-minute physical activity and sedentary behavior using previously validated cut points [32,33]. A cut point is an activity count value that corresponds to a designated intensity level (e.g., light, moderate, and vigorous intensity). This accelerometer has been validated as an accurate measure of frequency, intensity and duration of physical activity [32,34]. More recently it has been used to estimate time in sedentary behaviors [33] and it is also possible to examine patterns of transitions between behaviors (e.g., from sedentary to higher intensity activities) [35]. It also provides an independent (i.e., distinct form pedometer data collected during the intervention, see below) estimate of steps/day and cadence (steps/min) [10,36].

### Interventions

#### *Common program elements*

Both pedometer-based physical activity interventions implemented in WalkMore will be modeled off the success of the First Step Program [37]. Throughout the trial, and regardless of intervention group assignment, participants monitor their own daily community-based walking using pedometers and attend weekly meetings to review the previous week’s walking behaviours, discuss preferred strategies for success, and recommit to goals. The meetings with the interventionist will primarily be group-based, but accommodations will be made for individual meetings as necessary. Participants will be given pedometers and instructions focused on goal-setting and problem-solving, as well as calendars for self-monitoring and recording steps/day. Each meeting (held in a non-clinical setting) will also include a short walk (with options for being outside or inside, as weather permits). Participants will be taught how to monitor their own behavior, compute their own average steps/day each week (and time in moderate or greater intensity if this is their particular group assignment, see below), and recognize relapse (defined as not achieving their steps/day and/or time in moderate or greater intensity activity on any single week). Participants will also be encouraged to develop and share (with interventionists and with peers in their group meetings) their own strategies for achieving their goals.

For intervention tracking purposes, we have selected to use the NL-1000 distributed in the U.S. by New Lifestyles, Inc. The NL-1000 is a piezoelectric pedometer that is considered more accurate than the more commonly used Yamax pedometer in detecting steps/day in obese individuals [38] who we anticipate will form a large proportion of recruited participants. Further it has an on-board 7-day memory, allowing us to verify participant records for the same time period.

### BASIC vs. ENHANCED Interventions

Participants assigned to the BASIC intervention (10,000 steps/day with no guidance with regards to walking intensity/speed/cadence) may accumulate their daily steps in any manner they prefer (e.g., attending a mall walking program, walking children to school, walking at work, walking for errands, etc.). There will be absolutely no emphasis on intensity of walking. They will track their behavior using the NL-1000 but will never be shown the function that allows tracking of time in moderate or greater intensity activity.

Participants in the ENHANCED intervention will also be instructed to take 10,000 steps/day, but in addition will be encouraged to take make at least 3,000-4,000 of these steps at moderate or greater intensity (i.e., at a cadence of at least 100 steps/min) in order to achieve a daily goal of 30 minutes in moderate or greater intensity. They will track their behavior, both steps/day and time in moderate or greater intensity, using the NL-1000. We plan to verify records for the previous 7 days each time participants in the two intervention groups meet with the interventionist.

### Control group

Participants allocated to the control group will be asked to continue living their lifestyle as usual and to report back for a final assessment at 3 months.

### Adherence plan

We are defining acceptable adherence to the study protocol as averaging their goal steps/day (and/or time in moderate or greater intensity) at least 5 days/week and 83% of the weeks on study. The process of averaging steps/day over a week allows flexibility in being able to make up for lower days by having higher days. Further, participants will be excused from meeting their assigned steps/day goal up to 2 weeks during the 3-month long trial. For example, an individual assigned to the 10,000 steps/day condition would be expected to average 10,000 steps/day for at least 10 weeks of the 12 weeks on trial to be adherent. This provides time for vacations, illness, and other family and work commitments.

Everyone, including participants allocated to the control condition, will receive a pedometer upon study completion. We will also provide a total incentive of up to $100 US per individual as compensation for their time participating in the study; participants often must take off time to attend clinic assessments and this nominal compensation is appropriate. The $100 incentive is not awarded at one time but, is delivered as the participant progresses through the study. All participants will be able to earn this payment by adhering to study requirements, including meeting the 83% target adherence rate in order to receive the entire $100. The participants will receive $50 ($25 check per visit) for completion of both the baseline (0 month) and the 3 month assessment visit. From week 3 to week 12 of both walking interventions, participants will receive an additional $5 for every week they average at least 10,000 steps/day. Control participants will receive the additional $50 for remaining in the study for its duration.

### Statistical power and sample size

In the RCT conducted by Moreau et al. [20], mean resting systolic blood pressure among postmenopausl women was reduced by 6 mm Hg after a 12-week walking program. Likewise, in the comparative-effectiveness trial conducted by Seals et al. [39], mean resting systolic blood pressure was reduced by 5 mm Hg in postmenopausal women after a 13 week walking program. Based upon data presented by Seals et al. [39], we estimated that the standard deviation of systolic blood pressure change in WalkMore will be 6 mm Hg. Thus, a net of 42 completers per each intervention group and 17 completers in the control group will be required to detect a minimum 6 mm Hg difference in systolic blood pressure change for any comparison (Basic vs. Enhanced, Basic vs. Control, and Enhanced vs. Control) at 80% power while maintaining global α = 0.05 (0.05/3 = 0.01667 for each of the 3 possible comparisons). Assuming a maximum attrition of 15%, 120 participants will be enrolled in the study. We will randomize 50 participants into the BASIC group, 50 participants into the ENHANCED group, and 20 participants into the Control group.

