### Statistical analysis

The primary analysis will be on changes in systolic blood pressure at 12 weeks, comparing the 2 intervention groups relative to the control condition. Summary statistics (mean, standard deviations, ranges, medians, proportions) will be calculated for systolic and diastolic blood pressures and all other outcome variables of interest. Variables will be log-transformed as needed, to better approximate Gaussian distributions. Mixed effects statistical models will be employed to analyze the fixed effects of interventions and the random effects of subjects with respect to outcome trajectories across time. Analysis of reduction in response (e.g., blood pressure) will employ analysis of covariance to account for baseline variability. We will use graphical techniques (scatter and box-plots) to elicit associations and trends in the data and to guide the development of appropriate models. Standard diagnostics (residuals, goodness-of-fit tests) will assess model adequacy. All computations will be conducted with the statistical software package SAS version 9.3 (SAS Institute, Cary, NC).

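### The fixed 0.05/3 split is valid but gives away some power: with exactly three groups a closed test, or Holm, keeps the same 5% family-wise error (optional improvement)

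*Protocol article*

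**What the plan says.** Protocol article, Statistical power and sample size: the trial is sized on "a net of 42 completers per each intervention group and 17 completers in the control group". The target, 6 mm Hg with 80% power, applies to all three pairs of groups. Alpha is divided equally over those pairs: "while maintaining global α = 0.05 (0.05/3 = 0.01667 for each of the 3 possible comparisons". On the spread of the outcome the section says "we estimated that the standard deviation of systolic blood pressure change in WalkMore will be 6 mm Hg".

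Protocol article, Statistical analysis: the primary analysis is described as "comparing the 2 intervention groups relative to the control condition". The section names mixed models and analysis of covariance. It gives no significance threshold and no step-down or closed procedure. The only multiplicity rule in the document is therefore the equal three-way split in the sizing section.

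**The concern.** The three pairwise null hypotheses are logically linked. If two of them are true, so is the third. So once any one is false, at most one of the other two can still be true. An equal split ignores this and charges every contrast for three tests, even when only one true null can remain.

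The trial is small. The control group is expected to keep only 17 completers, which limits both control contrasts. The Abstract and Discussion make intensity added to volume the trial's question, so ENHANCED vs BASIC matters too. Both of those arms aim at 10,000 steps/day, and the protocol cites a 5 to 6 mm Hg reduction for a whole walking programme. The increment from intensity could therefore be below 6 mm Hg, and a stricter threshold costs most power at such intermediate differences.

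**Working it through.** **Inputs from the protocol.** SD of change 6 mm Hg; difference 6 mm Hg; completers 42 BASIC, 42 ENHANCED, 17 Control; alpha 0.05/3 = 0.01667 per contrast; power 80%; attrition 15%. Sidedness is not stated, so two-sided tests are assumed.

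**Step 1: the plan's own figures.** Normal approximation: power = Φ(δ/SE − z), with SE = SD·√(1/n₁ + 1/n₂) and z = 2.394 for two-sided 0.01667.

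- 42 vs 17: SE = 6·√(1/42 + 1/17) = 1.725; 6/1.725 − 2.394 = 1.085; power 86.1% (84.1% by exact t).
- 42 vs 42: SE = 6·√(2/42) = 1.309; 6/1.309 − 2.394 = 2.188; power 98.6% (98.2% by exact t).
- At a 2.5:1 ratio the exact t-test needs 16 controls and 40 per intervention arm (81.5% power). The stated 17 and 42 are slightly above that.
- Attrition: 42/0.85 = 49.4, rounded up to 50; 17/0.85 = 20; 50 + 50 + 20 = 120.

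The sample size is adequate at 0.01667.

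**Step 2: why the closed test is valid.** With three groups, the intersection of any two pairwise nulls is the global null that all three means are equal. The closed family is thus the global null plus three single pairs. A 2-df test of the global null at 0.05, then each pair at 0.05, controls the family-wise error strongly at 0.05. Holm controls it for any set of hypotheses.

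**Step 3: ceiling on the gain for ENHANCED vs BASIC.** No such procedure can do better than testing at 0.05 instead of 0.01667. At 3 mm Hg, 3/1.309 = 2.291, so power goes from Φ(2.291 − 2.394) = 45.9% to Φ(2.291 − 1.960) = 63.0%. By exact t it is 44.3% to 62.0%. The ceiling peaks near 2.9 mm Hg, at 17.7 points by exact t. The difference detectable with 80% power falls from 4.3 to 3.7 mm Hg.

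**Step 4: simulation.** 300,000 trials per scenario, SD 6, 42/42/17, pooled-variance t-tests on 42 + 42 + 17 − 3 = 98 degrees of freedom. Scenarios are true mean changes (Control, BASIC, ENHANCED) in mm Hg. The three pairs cannot all differ by exactly 6 in one ordering; (0, −6, −12) puts 6 on both BASIC vs Control and ENHANCED vs BASIC.

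| Scenario | Contrast | 0.05/3 | Holm | Closed |
|---|---|---|---|---|
| (0, −6, −12) | BASIC vs Control | 84.8% | 93.1% | 93.1% |
| (0, −6, −12) | ENHANCED vs BASIC | 98.3% | 99.5% | 99.5% |
| (0, −6, −6) | BASIC vs Control | 84.9% | 87.2% | 90.1% |
| (0, −6, −9) | ENHANCED vs BASIC | 44.7% | 61.0% | 62.1% |
| (0, −3, −6) | ENHANCED vs BASIC | 44.5% | 53.4% | 61.3% |
| (0, 0, −3) | ENHANCED vs BASIC | 44.6% | 46.2% | 52.4% |

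The last three rows assume a 3 mm Hg ENHANCED-BASIC difference, which the protocol does not give. There the closed test gains 17.4, 16.8 and 7.8 points, and Holm 16.4, 8.9 and 1.6.

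**Step 5: error rates.**

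| True state | False rejection | 0.05/3 | Holm | Closed |
|---|---|---|---|---|
| (0, 0, 0) | any contrast | 4.3% | 4.3% | 4.95% |
| (0, −6, −6) | ENHANCED vs BASIC | 1.7% | 4.2% | 5.0% |
| (0, 0, −6) | BASIC vs Control | 1.7% | 4.1% | 5.0% |

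All stay within the stated global 5%.

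**The case against.** Nothing in the protocol is stated wrongly: the equal split controls the family-wise error and the sample size holds. That stands, and it rules out a reading some may be tempted to make, that the plan contains an error or that the trial is too small because of the split.

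The 0.01667 appears in the sizing section, and the analysis section fixes no threshold. Sizing at 0.05/3 and then testing by a closed procedure would contradict neither section, and an analysis plan not shown may already do this. That also stands. What remains is that the document at hand states this one rule and no other.

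A reader might infer that 17 points are lost on the intensity contrast as a matter of course. The protocol does not support that. Its only figure for that contrast is 6 mm Hg with SD 6, where the gain is about 1 point. The larger figure needs a true difference near 3 mm Hg, almost exactly where the gain peaks. A difference below 6 is plausible but remains an assumption.

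A reader might also infer that the split buys no extra error protection. That is so only against the 5% family-wise target. On a single true null it holds the error at 1.7% instead of 4 to 5%, and its simultaneous confidence intervals agree with its decisions.

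Finally, the two sections differ on the family: sizing counts three contrasts, while the primary analysis refers to the two against control. The family should be settled first. The closed test is valid either way, because the two control nulls together are again the global null.

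**Conclusion.** This is an optional, cheap efficiency improvement, not an error. At the protocol's own effect and SD, the useful gain is on BASIC vs Control: from about 85% to 93% if ENHANCED is a further 6 mm Hg lower, and to about 90% (Holm 87%) if ENHANCED equals BASIC. The intensity contrast gains only about 1 point at 6 mm Hg. It gains about 8 to 17 points with the closed test, or 2 to 16 with Holm, if the true difference is 3 mm Hg.

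The two procedures are not interchangeable: Holm falls well behind when a control contrast is weak, so the closed test is preferable. These figures rest on two-sided pooled-variance tests of change, SD 6 and exactly 42/42/17 completers. The 3 mm Hg difference is the review's assumption.

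**What to change.** Add one sentence to Statistical analysis, for example: *The three pairwise contrasts in change in systolic blood pressure are tested by a closed procedure: a global 2-df test of group at two-sided 0.05 and, only if it is significant, each pairwise contrast at two-sided 0.05.* Holm on the three p-values is the acceptable alternative. Say there which contrasts form the family, so that the section agrees with the sizing section. Leave 0.05/3 in Statistical power and sample size, described as the conservative basis of the sample size only.

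No extra participants are needed, and the change should be made before unblinded data are seen. It has two costs. Confidence intervals no longer correspond exactly to the stepwise decisions, so report 95% intervals beside adjusted p-values and say that the intervals are not simultaneous. The false-positive rate on a single true null rises from 1.7% to at most 5%, which is still within the global alpha that the protocol sets.

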### Statistical analysis

The primary analysis will be on changes in systolic blood pressure at 12 weeks, comparing the 2 intervention groups relative to the control condition. Summary statistics (mean, standard deviations, ranges, medians, proportions) will be calculated for systolic and diastolic blood pressures and all other outcome variables of interest. Variables will be log-transformed as needed, to better approximate Gaussian distributions. Mixed effects statistical models will be employed to analyze the fixed effects of interventions and the random effects of subjects with respect to outcome trajectories across time. Analysis of reduction in response (e.g., blood pressure) will employ analysis of covariance to account for baseline variability. We will use graphical techniques (scatter and box-plots) to elicit associations and trends in the data and to guide the development of appropriate models. Standard diagnostics (residuals, goodness-of-fit tests) will assess model adequacy. All computations will be conducted with the statistical software package SAS version 9.3 (SAS Institute, Cary, NC).

## Discussion

Capitalizing on the appeal of walking as a feasible behavior for the vast majority of the population and the practicality of pedometer-based programming, WalkMore is designed to evaluate the comparative effectiveness of increasing ambulatory physical activity with and without an emphasis on its intensity on blood pressure in sedentary postmenopausal women. This study will inform public health and health promotion efforts to deliver clear and actionable physical activity messages related to improving blood pressure in a subpopulation at increased risk of cardiovascular disease. This study will also yield insights into the extent to which secondary outcomes are affected by increased ambulatory physical activity with and without an emphasis on its intensity.
